### 6.5.3 Adverse Reaction

The most common adverse reactions (incidence  $\geq 25\%$ ) are: cutaneous adverse reactions (including rash, pruritus, and nail changes), headache, diarrhea, and infection. Please refer to the instructions of the cetuximab label for other adverse drug reactions.

[REDACTED]

### 6.7 Concomitant Medications/Treatments

Any prescription or over-the-counter (OTC) drug product other than study drugs should be discussed with the investigator to be sure there is no potential interference with study drugs, avoid their use during the study if possible. Medications or vaccinations specifically prohibited in the exclusion criteria are not allowed during the ongoing trial. No recreational or addictive drugs, herbal remedies, self-prescribed drugs, or excessive alcohol should be used during the study. If considered necessary for the subject's well-being, drugs for concomitant medical conditions or for symptom management may be given at the discretion of the investigator.

All concomitant medication will be recorded on the electronic case report form (eCRF) including, but not limited to, all prescription, OTC, herbal supplements and intravenous medications and fluids. If changes occur during the study, documentation of drug dosage, frequency, route and date will also be recorded on the eCRF. All concomitant medications received within 28 days prior to the first dose of study treatment and up to 30 days after the last dose of study intervention should be recorded. All concomitant medications administered during SAEs are to be recorded.

#### 6.7.1 Prohibited Concomitant Therapy (during treatment and within 28 days after drug discontinuation)

Patients should not receive other anti-tumor therapy while on treatment in this study, i.e. surgery, radiotherapy therapy, cytotoxic, biological, Chinese herbal medicine with anti-tumor indication, or hormonal other than replacement. Exception can be made for localized palliative radiotherapy for symptom control provided that the localized palliative radiotherapy does not compromise tumor assessments of target lesions. Other anti-tumor treatments should not be administered until

disease progression (as per clinical practice standards at the study center), unmanageable toxicity or no further clinical benefit occurs which requires permanent discontinuation of D-1553.

Patients are not allowed to take the following medications, except for management of AEs as advised by the Principal Investigator. Patients must stop taking these drugs for at least 14 days before dosing, except coumarin anticoagulants that can be stopped one week before inclusion (heparin of low molecular weight is acceptable):

- Any strong inhibitor and inducer of CYP3A4 used 2 weeks before inclusion and during the trial treatment phases (e.g. ketoconazole, clarithromycin, indinavir, itraconazole, etc. refer to [Appendix 4](#); however, this list may be not comprehensive, additional information may be obtained from the IFU of these drugs). In addition, herbals/supplements containing St. John's wart (*Hypericum perforatum* L.) and Seville orange etc. should also be avoided.
- [REDACTED]
- Any medications which can prolong QT interval or cause torsade de pointe (Refer to [Appendix 4](#)).

[REDACTED]

[REDACTED]

[REDACTED]

[REDACTED]

[REDACTED]

In the interest of patients' safety and acceptable standards of medical care, the Investigator will be permitted to prescribe the treatment(s) at his/her discretion.

#### Hematologic Support

For Phase 1b and Phase 2, hematologic support may be administered as medically indicated (e.g., blood transfusions, granulocyte-stimulating factor (G-CSF), erythropoietin stimulating agents) according to the institutional site standard. If there are no standard procedures for the use of growth factors, the American Society of Clinical Oncology [ASCO] Guidelines for Use of Hematopoietic Colony-Stimulating Factors, available at [www.asco.org](http://www.asco.org), will be followed.

#### Management of Diarrhea

For Phase 1b and Phase 2, prophylactic treatment for diarrhea is permitted during the study if clinically indicated according to the institutional guidelines. If there are no institutional standards, refer to the guidelines published by Benson, et al. (39) in Journal of Clinical Oncology.

#### Management of Nausea/Vomiting

Antiemetics may be administered as clinical indicated. If there are no institutional standards, refer to the ASCO guidelines for Antiemetics in Oncology (40).

#### Effective Contraception

Combined (estrogen and progestogen containing) hormonal contraception associated with inhibition of ovulation:

- Oral
- Intravaginal
- Transdermal

Progestogen-only hormonal contraception associated with inhibition of ovulation:

- Oral

- Injection
- Implantable

Intrauterine device (IUD)

Intrauterine hormonal-releasing system (IUS)

Bilateral tubal occlusion

Vasectomized partner with documentation of the success of the vasectomy

Complete abstinence from heterosexual intercourse (periodic abstinence is not a safe method)

Male patients with partners who are WOCBP should use a combination of male condom with cap, diaphragm, or sponge with spermicide during the trial and for 6 months after the last dose of D-1553.

[REDACTED]

[REDACTED]

[REDACTED]

[REDACTED]

[REDACTED]

[REDACTED]

[REDACTED]

[REDACTED]

[REDACTED]

## 6.9 Compliance

When subjects are dosed at the site, they will receive study intervention directly from the investigator or designee, under medical supervision. The date and time of each dose administered in the clinic will be recorded in the source documents and recorded in the eCRF. The dose of study intervention and study subject identification will be confirmed at the time of dosing by a member of the study site staff other than the person administering the study intervention.

When subjects self-administer study intervention(s) at home, compliance with study intervention will be assessed at each visit. Subjects should record the dose and time of study intervention in a diary distributed by the study site. The diary will be reviewed by the study staff during the site visits and documented in the eCRF. Deviation(s) from the prescribed dosage regimen should be recorded in the eCRF.

A record of the number of D-1553 tablets [REDACTED] dispensed to and taken by each subject must be maintained and reconciled with study intervention and compliance

records. Intervention start and stop dates, including dates for intervention delays and/or dose reductions will also be recorded in the eCRF.

## **7 STUDY PROCEDURES**

Study procedures and their time points are summarized in the Schedule of Assessments (see Table 1-1 through Table 1-3). Refer to the investigational product, laboratory and site imaging manuals for detailed collection and handling procedures.

Adherence to the study design requirements, including those specified in the Schedule of Assessments, is essential and required for study conduct.

A signed and dated IRB/IEC approved ICF must be obtained prior to performing any study specific procedures, including discontinuing standard therapy for observing study specific washout periods.

Subjects will be seen in the clinic for study evaluations. During all visits' invasive procedures like blood draws or biopsies should be completed after ECGs and vital signs.

Blood samples for biomarker and PK assessments should be drawn from a peripheral vein and not from a central venous catheter. The study specific lab manual will provide additional detail on lab sampling and handling requirements.

Furthermore, start of a treatment can be delayed for administrative/logistical reasons for up to 7 days to allow for appropriate scheduling after discussion with and final approval by sponsor.

Any missed visits, tests not done, or examinations that are not conducted must be reported as such on the eCRFs. Subsequent study visits should resume on the original schedule. Missed assessments at prior visits should not be duplicated at subsequent visits. Every effort should be taken to collect all biomarker and PK samples as described in the schedule of assessments.

Additional procedures deemed necessary as part of standard of care or as required by local laws and regulations may be performed at the Investigator's discretion.

At selected sites, up to a total of 30 phase 2 subjects will also be consented to have intensive PK and ECG data collected according to Table 1-6.

### **7.1 Phase 1 Procedures**

#### **7.1.1 Phase 1 - Screening Procedures (Day-28 To Day -1)**

All subjects will be screened for eligibility and have a repeat brief pre-dose assessment conducted prior to the first dose of D-1553 to confirm eligibility. The following screening assessments must be performed within 28 days (unless otherwise noted) before enrollment:

- Written informed consent, must be obtained prior to undergoing any study procedure and may occur prior to the 28-day screening period
- Medical history review
- Diagnosis, history of solid tumor

- Demographics
- Physical examination, body weight and height
- Assessment against inclusion/exclusion criteria
- Pregnancy test which must be performed within 24 hours prior to initiation of first treatment. Pregnancy test is required for female subjects with childbearing potential.
- ECOG performance status
- Assessment of KRASG12C status
- Vital signs, including temperature, pulse, respiratory rate and blood pressure
- Laboratory test (including hematology, blood chemistry, urinalysis, coagulation, etc.)
- ECG (12-lead) performed in a recumbent position after 5 minutes of rest, collected in triplicate and read by central laboratory
- [REDACTED]
- [REDACTED]
- [REDACTED]
- Tumor assessment (screening scans within 6 weeks prior to Day 1 of treatment cycle 1 are allowed, even if they are performed before the subject decides to join the study, to avoid radiation risk from extra scans)
- Prior/concomitant medication review
- Testing for HIV, Hep B and Hep C should be conducted during Screening for eligibility determination. A positive HBsAg will be considered positive for Hep B. A positive anti-HCV antibody and anti-HIV antibody will be considered positive for Hep C and HIV, respectively. [REDACTED]  
[REDACTED]

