4. Demographic data includes age, sex and race/ethnic group as indicated by the subject.
5. Physical examination includes major body systems. Body weight will be recorded at screening and Day 1 of each treatment cycle. Height will only be measured at Screening.
6. Inclusion and exclusion criteria must be evaluated prior to first dose of study intervention.
7. Serum or urine pregnancy tests will be performed at Screening, Pre-Dose Day -1 and End of Treatment or Withdrawal as well as on Day 1 of every odd-numbered cycle (except Cycle 1). Subjects with a positive pregnancy test will be permanently discontinued from treatment with study intervention and will enter into a safety follow-up period.
8. ECOG performance status grade is available in [Appendix 1](#) of the protocol.

9. KRASG12C mutation status must be documented for the purpose of the inclusion criteria using a blood or tumor tissue sample and can be from a previously conducted local laboratory test result up to 5 years prior to this study. The method used for the test should also be collected.
10. Vital signs include body temperature, pulse, respiratory rate and blood pressure. These should be done once pre-dose and once post-dose on dosing days, and once on non-dosing days (pre- and post-dose procedures in BID cohort will only be required for the first dose during the day). Both pre-dose and post-dose measurements can have 1-hour window.
11. Laboratory assessments includes hematology, blood chemistry, urinalysis and coagulation. Weekly or more frequent tests may be given at the investigator's discretion:  
Hematology includes complete blood count including RBC, hemoglobin, hematocrit, WBC and differential (neutrophils, eosinophils, basophils, lymphocytes, monocytes and other cells) and platelet count. Blood chemistry includes total, direct and indirect bilirubin, ALT, AST, ALP, LDH, total protein, albumin, sodium, potassium, magnesium, chloride, calcium, phosphorus, BUN, creatinine, uric acid, glucose. Additional blood chemistry tests may be performed as clinically indicated (e.g., amylase, lipase, creatinine kinase, GGT). Urinalysis includes pH, specific gravity, protein, glucose, ketones, RBC, WBC, bilirubin. Additional analyses may be required as clinically indicated. Coagulation parameters should be determined throughout the study when clinically indicated, including aPTT and INR.

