16. Radiologic imaging will be used for tumor assessment. A CT scan (with or without contrast) of the chest, abdomen and pelvis will be performed to assess metastatic disease. A bone scan will be performed in the event of clinical symptoms of bone metastases. A baseline brain MRI (with or without contrast; CT is acceptable if MRI is contradicted), should be performed for subjects with a history of or suspected to have CNS metastases. For subjects with no CNS metastases at baseline, it is not necessary to repeat brain MRI unless CNS involvement is suspected during the study. Screening scans can be performed within 6 weeks prior to Day 1 of treatment cycle 1. Tumor assessment will be performed during screening and at the completion of every 2 treatment cycles for the first 8 treatment cycles, thereafter at the end of every 3 treatment cycles until disease progression, start of new anticancer treatment, death, withdrawal of consent, or until end of study. There is a  $\pm 7$ -day window for each tumor assessment. For PFS, subjects who do not have disease progression on study will be followed for tumor assessment, approximately every 12 weeks ( $\pm 2$  weeks), until disease progression, death, lost to follow-up, start of another anticancer therapy, or other reasons that a follow-up is not possible.
17. These procedures can be done on Day -1 or Day 1 but have to be completed prior to first dose of study intervention. They are intended for checking the subject status before the first dose, not for eligibility. A subject's eligibility should be determined during the screening period. Laboratory tests performed in the screening period within 7 days of Day 1 do not need to be repeated on Day -1 or Day 1 unless clinically indicated.
18. These visits need to be completed within 7 days of the last dose of study intervention:
  - a. Subjects who stop treatment due to disease progression at the visit time do not need to repeat the imaging examination;
  - b. The radiologic imaging examination needs to be repeated if more than 4 weeks have passed from the last examination to the end of treatment visit;
  - c. Other examinations are required to be repeated if more than 1 week from last examinations.
19. [REDACTED]

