
[REDACTED]

14. Subject has any other known primary malignancy that is progressing or has required active treatment within the past 3 years. Note: subjects with basal cell carcinoma of the skin, squamous cell carcinoma of the skin, or carcinoma in situ (e.g., breast carcinoma, cervical cancer in situ) that have undergone potentially curative therapy are not excluded.

15. Subject is pregnant or lactating.

16. [REDACTED]

- [REDACTED]  
[REDACTED]
- [REDACTED]  
[REDACTED]  
[REDACTED]
- [REDACTED]  
[REDACTED]
- [REDACTED]  
[REDACTED]  
[REDACTED]  
[REDACTED]  
[REDACTED]
- [REDACTED]  
[REDACTED]
- [REDACTED]  
[REDACTED]
- [REDACTED]
- [REDACTED]  
[REDACTED]  
[REDACTED]  
[REDACTED]

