#### 7.1.2 Phase 1 – Pre-dose Assessment (Day-1 To Day 1)

The results from the screening visit evaluations will be reviewed to ensure the subject eligibility. The following procedures will be performed on Day -1 after check-in or the morning of Day 1 prior to dosing for all subjects:

- Reassessment of inclusion/exclusion criteria by review of all screening results and repeating any test if needed
- Physical examination, including body weight

- Vital signs, including temperature, pulse, respiratory rate and blood pressure
- Laboratory and pregnancy tests (tests performed in the screening period within 7 days of Day 1 do not need to be repeated on Day -1 or Day 1 unless clinically indicated). Pregnancy test is required for female subjects with childbearing potential
- [REDACTED]
- AE assessment
- Concomitant medication review

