### 7.2.3 Phase 2 – Pre-dose Assessment (Day -1 To Day 1)

The results from the screening visit evaluations will be reviewed to ensure the subject eligibility. The following procedures will be performed on Day -1 after check-in or the morning of Day 1 prior to dosing for all subjects:

- Reassessment of inclusion/exclusion criteria by review of all screening results and repeating any test if needed
- Physical examination, including body weight
- Vital signs, including temperature, pulse, respiratory rate and blood pressure
- Laboratory and pregnancy tests (these tests performed in the screening period within 7 days of Day 1 do not need to be repeated on Day -1 or Day 1 unless clinically indicated). Pregnancy test is required for female subjects with childbearing potential
- [REDACTED]
- AE assessment
- Concomitant medication review

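### The 7-day no-repeat allowance in Sections 7.1.2 and 7.2.3 covers pregnancy tests and so contradicts the protocol's own 24-hour rule before first dose

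*Protocol*

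**What the plan says.** Four places in the protocol set the timing of the pregnancy test before treatment.

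- **Sections 7.1.1 (Phase 1) and 7.2.2 (Phase 2), screening lists:** "Pregnancy test which must be performed within 24 hours prior to initiation of first treatment".
- **Section 7.1.2, Phase 1 pre-dose list:** "Laboratory and pregnancy tests (tests performed in the screening period within 7 days of Day 1 do not need to be repeated". The only exception is a clinical reason to test again.
- **Section 7.2.3, Phase 2 pre-dose list:** the same allowance, "Laboratory and pregnancy tests (these tests performed in the screening period within 7 days of Day 1 do not need to be repeated".
- **Schedule of Activities, footnote 7 of Tables 1-1 to 1-4:** "Serum or urine pregnancy tests will be performed at Screening, Pre-Dose Day -1 and End of Treatment or Withdrawal", plus Day 1 of odd-numbered cycles after Cycle 1.

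The Schedule also has a 7-day allowance of its own (footnotes 17, 22, 18 and 23 of Tables 1-1 to 1-4 respectively). It reads "Laboratory tests performed in the screening period within 7 days of Day 1 do not need to be repeated" and does not mention pregnancy tests. Footnote 11 gives the content of that category: "Laboratory assessments includes hematology, blood chemistry, urinalysis and coagulation". The pregnancy test has a separate row and footnote.

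Three other provisions bear on the point. Exclusion criterion 15 in Section 5.2 is "Subject is pregnant or lactating". Section 8.4 warns of possible harm to a fetus from D-1553, alone or combined with other therapies. Section 7 provides that "start of a treatment can be delayed for administrative/logistical reasons for up to 7 days to allow for appropriate scheduling", subject to discussion with the sponsor and its final approval.

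**The concern.** The screening sections set a mandatory 24-hour limit. The pre-dose sections, which are the lists staff work from on Day -1 and Day 1, say that a test from the preceding week need not be repeated. A site that follows the pre-dose list as worded can breach the screening section while doing what the protocol told it to do. A monitor could not say cleanly whether that is a deviation.

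What is at stake is subject safety. The test enforces an exclusion criterion in a first-in-human study of a drug for which the protocol itself states a possible fetal risk. The 24-hour limit is a safeguard the sponsor chose, and the allowance weakens it.

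**Working it through.** The protocol gives no figure to reproduce here. The check compares the rules on the protocol's day scale, which has no Day 0: the windows run from Day -28 to Day -1 and then from Day -1 to Day 1.

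**Which rule accepts which test day**

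| Day of latest test | 24-hour rule (7.1.1, 7.2.2) | 7-day allowance (7.1.2, 7.2.3) | Schedule (footnote 7) |
|---|---|---|---|
| Day -8 or earlier | not accepted | repeat needed | Day -1 test needed |
| Day -7 to Day -2 | not accepted | **no repeat needed** | Day -1 test needed |
| Day -1 | accepted if no more than 24 hours before dosing | no repeat needed | accepted |

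**Size of the gap**

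- Days covered by the allowance: Day -7 to Day -1 = 7 days.
- Days the 24-hour rule can reach: Day -1 (and Day 1 before dosing).
- Covered by the allowance but outside the rule: Day -7 to Day -2 = 7 - 1 = 6 of 7 days.
- Age of the test at first dose: up to about 7 days, against a limit of 24 hours.

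**A route by which this can happen**

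Suppose the logistics delay in Section 7 applies to the first dose, and the test was done on the planned Day -1. After a delay of k days the test falls on Day -(1 + k):

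- k = 1 gives Day -2, and k = 6 gives Day -7. For k = 1 to 6 the test is more than 24 hours old but still inside the allowance.
- k = 7 gives Day -8, which is outside the allowance, so a repeat is required.

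**A smaller mismatch in the Schedule**

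Footnote 7 names Day -1 without a time. With illustrative clock times, a test at 08:00 on Day -1 and a dose at 10:00 on Day 1 are 24 + 2 = 26 hours apart. That meets footnote 7 but misses the 24-hour rule. The six-day count works in whole days and leaves out this part of Day -1.

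**The case against.** The strongest reply is that the texts can be read together. The 24-hour rule sits in the screening list, so a compliant screening test is already one taken within 24 hours. On that reading the pre-dose clause only spares a duplicate. It does not say that an older test suffices, and it does not lift the mandatory wording. A site that always tests within 24 hours complies with every section. This last point is correct. The reading itself fails, because it leaves the 7-day window with no meaning for pregnancy tests.

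Other points on that side:

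- *Both pre-dose bullets go on to say that the test is required for women of childbearing potential.* The same sentence stands in Sections 7.1.1 and 7.2.2. It says who is tested, not when.
- *Section 7 makes adherence to the Schedule mandatory, and the pre-dose lists call for eligibility to be reassessed.* The Schedule supports the strict rule, so this shows which text should prevail. It does not remove the conflicting one.
- *The Schedule's laboratory tests might include pregnancy tests.* Footnote 11 and the separate row speak against this. The content of Appendix 2 is not available to settle it. Even if they were included, the conflict with the 24-hour rule would remain.
- *The delay route is conjecture.* It does depend on Section 7 covering the first dose, and it needs sponsor approval. The contradiction does not depend on it.
- *Contraception or abstinence is required from consent.* This lowers the risk but does not replace a test the protocol makes mandatory.

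**Conclusion.** The concern holds. Sections 7.1.2 and 7.2.3 contradict Sections 7.1.1 and 7.2.2 and depart from the Schedule. The wording of the Schedule suggests that including pregnancy tests in the allowance was a drafting slip.

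Six of the seven days covered by the allowance lie outside the 24-hour rule. This rests on there being no Day 0 and on reading the 7 days as Day -7 to Day -1. The people affected are women of childbearing potential whose latest test fell on Day -7 to Day -2 at a site that relies on the allowance. The protocol does not allow them to be counted. There is no effect on sample size, error rates or analysis. The point should be corrected because it concerns a safety check before first dose, although careful sites can already avoid the problem.

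**What to change.** 1. In Sections 7.1.2 and 7.2.3, take pregnancy tests out of the 7-day allowance so that it covers laboratory tests only, as in the Schedule.
2. Add a separate bullet to both sections, for example: *Serum or urine pregnancy test for women of childbearing potential no more than 24 hours before first dose. The 7-day allowance does not apply. A screening test taken inside these 24 hours need not be repeated.*
3. In footnote 7 of Tables 1-1 to 1-4, replace the Day -1 timing with: *pre-dose, no more than 24 hours before first dose (Day -1 or Day 1)*. This also removes the 26-hour mismatch.
4. Leave Sections 7.1.1 and 7.2.2 unchanged.

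The cost is two bullets and four footnotes reworded, and at most one extra urine or serum test for some women, which the protocol already requires elsewhere.
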